## Funding Sources:

**CANADIAN INSTITUTES OF HEALTH RESEARCH**

**HAMILTON ACADEMIC HEALTH SCIENCES ORGANIZATION**

## **1.0. INTRODUCTION**

Frailty can be characterized as a state of diminished reserves (energy, physical ability, cognition, health) to the extent that function is reduced and the person is more vulnerable to external stressors (e.g., new medication or urinary tract infection) [1,2]. Our research suggests that approximately 23% of Canadians over age 65 are frail [3] and by age 85 this estimate increases to over 40% [4]. Older adults who are frail are high users of healthcare services [5] and those with moderate or severe frailty have an 8-fold greater relative risk of institutionalization (95% CI= 4.9-15.2) [6]. Thus, within our rapidly aging society, **there is a clear need for feasible, effective and sustainable community-based models to address the enormous problem of managing frailty.**

Two important considerations about frailty from a management perspective are: 1) frailty is **dynamic in nature (i.e., may improve or worsen over time)** [7] and 2) frailty is **reversible or treatable** [8]. Although frailty consensus recommendations [9] suggest treatment with specific modalities (exercise; reduction of polypharmacy; vitamin D3; protein supplementation), there is little evidence regarding whether a targeted, community-based approach can improve frailty or prevent decline and whether additional management approaches are required over and above exercise. Drawing on the principles of a standardized multi-modal approach in **cardiac** [10,11] and **cancer rehabilitation** [12,13], frailty rehabilitation could be an accessible community-based intervention with the **ultimate goal** to improve physical function, reducing frailty, and enabling independence within the community.

**The LIFE trial** which examined physical activity in sedentary adults had a relatively small number of "frail" adults and was focused on walking (up to 150 min/week) with only 10-min strength per session. However, the LIFE trial **did not meet the minimum criteria for 180 min/week of exercise** (with a high challenge to balance) recently identified effective for fall prevention [14]. **The Australian FIT trial** [15] a land-mark trial, demonstrated that multi-modal intervention significantly reduces frailty and was the first to demonstrate that treating frailty was a realistic therapeutic goal [8]. This intervention was **resource intensive and based within a geriatric/rehabilitation service**, which may not be feasible in many communities across Canada and given the wait-lists. The FIT trial was not able to determine the effects of exercise alone. **The Singapore FIT trial** [16] examined exercise, cognitive training, and nutritional supplementation separately versus multi-modal, however over 70% were pre-frail. This trial was not a model of multi-modal rehabilitation delivered in a community setting and did not include medication review (an important component for comprehensive frailty management). This trial was **not powered** to detect statistically significant differences between intervention-groups (i.e. the potential additive effect of the multi-modal intervention over individual interventions), however, a reduction in frailty was observed in the multi-modal intervention group compared to the control group (OR=5.00, 95% CI=1.88-13.3). **Our pilot work** has demonstrated the feasibility of community-based frailty interventions in Canada without the use of specialized assessment teams. With the high co-occurrence of frailty and cognitive impairment [17], we have demonstrated individuals with mild to moderate cognitive decline can successfully participate in group exercise. Thus, our next step is a larger-scale trial to definitively consider the effectiveness of such an approach compared to less intensive interventions. Building upon our previous research, our aim is to consider if frailty rehabilitation is feasible and effective for a large proportion of older adults living with frailty who are community-dwelling (i.e., not housebound and able to follow instructions to

## FRAILTY REHABILITATION: A COMMUNITY-BASED INTERVENTION TO PROMOTE HEALTHY AGING

participate in the group). More specifically, this trial is the first of its kind to examine a **model of frailty rehabilitation** (that could be implemented within the community) and extends the previous literature. The frailty rehabilitation study will be publicly known as the OPTIMAL Fitness study to include positive language associated with aging to assist with recruitment of community-dwelling older adults.

**Frailty and Sarcopenia:** While there is some overlap between sarcopenia and frailty, sarcopenia may be the precursor to frailty. Recent consensus guidelines define sarcopenia as a muscle disease (“muscle failure”) with low strength, low muscle quantity and low physical performance (17). According to the European Working Group on Sarcopenia in Older People (EWGSOP), approximately 50 million people currently live with sarcopenia worldwide and is projected to increase to 200 million in the next 40-years (17). Sarcopenia is associated with increased fall-risk, fractures, mobility disability, loss of independence and reduced quality of life. Furthermore, older adults with sarcopenia are 5x more likely to have increased hospital costs compared to those without sarcopenia (OR = 5.70, 95% CI 1.57–20.71). Therefore, optimal care of older adults with sarcopenia is essential to reduce the personal, social and economic costs when untreated (17). Building upon our CIHR RCT, we aim to understand which components of a functional rehabilitation program are essential to change the trajectory of sarcopenia in older adults with sarcopenia.

## 2.0. OBJECTIVES

|           |                                                                                                                                                                                                                                                                                                                                                                               |                                                                                                                                                                                                                                                                                                                                                                                                                                                                                                                                                                                                                                                                                                                                           |
|-----------|-------------------------------------------------------------------------------------------------------------------------------------------------------------------------------------------------------------------------------------------------------------------------------------------------------------------------------------------------------------------------------|-------------------------------------------------------------------------------------------------------------------------------------------------------------------------------------------------------------------------------------------------------------------------------------------------------------------------------------------------------------------------------------------------------------------------------------------------------------------------------------------------------------------------------------------------------------------------------------------------------------------------------------------------------------------------------------------------------------------------------------------|
| PRIMARY   | In community-dwelling older adults living with frailty and sarcopenia, does a 4-month multi-modal intervention (Arm 3) improve physical function (Short Physical Performance Battery and 400-m Walk Test) compared with control (Arm 1) and group exercise alone (Arm 2)?                                                                                              | HYPOTHESES: 
 
- Frailty rehabilitation will achieve the most successful results in frail and sarcopenic cohorts and offer enhanced benefits relative to the other arms. Socialization and exercise only will provide clinically meaningful improvements to physical function and frailty over time, with exercise alone achieving greater benefits than control (usual care).
 
- Frailty rehabilitation will result in greater reductions in healthcare utilization in frail and sarcopenic older adults relative to the other arms.
 
- A range of functional abilities and health-related quality of life will be identified in older adults living with frailty.
 
 |
| SECONDARY | To better understand the functional abilities (frailty; fear of falling; fitness; strength; cognition; health-related quality of life; life space mobility; activities of daily living; depression/mood; nutrition) of older adults living with frailty and sarcopenia and translate the first Canadian model of frailty and sarcopenia rehabilitation and management. |                                                                                                                                                                                                                                                                                                                                                                                                                                                                                                                                                                                                                                                                                                                                           |
|           | Determine which components of a functional rehabilitation program are essential to change the trajectory of sarcopenia ( muscle mass; muscle strength; muscle function ).

Determine the feasibility of a functional rehabilitation program ( recruitment rate, retention rate, data collection, adherence to all interventions ).                        |                                                                                                                                                                                                                                                                                                                                                                                                                                                                                                                                                                                                                                                                                                                                           |

|                    |                                                                                                                                                                                                                                                                              |  |
|--------------------|------------------------------------------------------------------------------------------------------------------------------------------------------------------------------------------------------------------------------------------------------------------------------|--|
| EXPLORATORY | Does a 4-month multi-modal intervention (Arm 3) reduce healthcare utilization (emergency room visits; hospitalization; home care service use; institutionalization) compared with control (Arm 1) and group exercise alone (Arm 2) during a 6-month follow-up period? |  |
|--------------------|------------------------------------------------------------------------------------------------------------------------------------------------------------------------------------------------------------------------------------------------------------------------------|--|

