**4.5. Randomization:** Stratified block randomization (1:1 randomization ratio) with the allocation sequence generated by a computer will be used to randomly allocate participants to their group assignment. Participants will be stratified based on their sex, age (<80 or  $\geq 80$  years), and location preference. Research staff will obtain informed consent and confirm eligibility and will randomize the participant using Research Electronic Data Capture (REDCap) randomization system, a secure web application for building and managing online surveys and databases. To protect against selection bias, the randomization sequence will be adequately concealed so that investigators/participants are not aware of the upcoming assignment. To protect against ascertainment bias, baseline measures will be assessed **prior** to randomization. Outcome assessors, the study biostatistician, the investigative team, and the steering committee will be blinded to intervention assignments. Research assistants, study intervention personnel (pharmacist, instructors) and participants will not be blinded.

**4.6. Interventions:** Participants will be randomized to one of three arms (control, group exercise only, multi-modal), with the intervention lasting 4-months (**Figure 1**). Each cohort will have at maximum, 11 people

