### **Arm 1: Control:**

Participants randomized to the control arm will not receive any of the Frailty Management Interventions (see Table 1).

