### **Arm 3: Multi-modal Intervention:**

**Group Exercise/Supplemental Home Exercise:** This will be delivered identically to Arm 2. **Oral Nutritional Supplementation:** As piloted in our Virtual Frailty Rehab Study, the ONS (each serving) contains 225kcal, and 11-12 grams protein (Glucerna, Ensure). Abbott Nutrition has provided support to this study in relation to the Abbott products Ensure® and Glucerna®. Participants are advised to take this with a meal or within 3 hours of exercise on activity days. Participants will be provided with two ONS each day of the study. The research staff will schedule Arm 3 participants for an initial and post assessment appointment. Working in consultation with the study geriatricians and pharmacist, as required, the multi-modal arm assessment will include: 1) Reviewing the participants' relevant medical and medication history at the baseline assessment (using the medical and medication history form completed and collected by study personnel). **Nutrition review:** Conduct nutritional screening flow (developed by a consultant dietician) and review any questions, provide some additional counseling/coaching at follow-up visits. ONS will be provided to all participants unless contraindicated. **Medication review:** Review/update current medication list (baseline medical history form) and forward the list and medical history to the consultant study pharmacist. Prior to the medication review, we will also be requesting permission from the participant to contact their family physician and community pharmacist to receive their medication list. The Beers and START/STOPP criteria will be considered to provide

PROTOCOL

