A blinded assessor with kinesiology/rehabilitation training (with assistance from a GERAS volunteer who will be trained on safety supervision) will perform study outcome assessments at Hamilton Health Science (piloted in our DANCE study). Data, with identifying information removed, will be securely stored in a locked cabinet in the locked research office, at the GERAS Centre at Hamilton Health Sciences. Electronic data will be entered and stored in a **REDCap (Research Electronic Data Capture) database**.

A subset of participants, from all 3 study arms, will be randomly selected to wear the study ActiGraph GT9X Link Accelerometer for the duration of the study. The device will collect raw acceleration data, physical activity intensity, total sleep time, activity bouts, sedentary bouts, sleep efficiency, and energy expenditure, in real time. **Sarcopenia outcomes:** All participants will be screened for sarcopenia at baseline. Physical performance based on the 5-time chair stand test with a score of greater than or equal to 12 seconds is predictive of sarcopenia [56]. Of the 324 participants, up to 75 of them with sarcopenia will undergo additional assessments. Aligned with the 2019 Asian Working Group for Sarcopenia Consensus on Sarcopenia and Treatment we will assess, confirm and grade the severity of sarcopenia at baseline and 4-months. Muscle mass will be assessed with readily available dual-energy x-ray absorptiometry (DXA), and the gold standard magnetic resonance imaging (MRI). Up to 75 participants with sarcopenia will be assessed with DXA (**Table 2**). Due to budget constraints, a subset of up to 36 participants will undergo an MRI scan in addition to DXA. Muscle strength will be assessed as grip strength and chair stand tests. Muscle function will be quantified by gait speed, short physical performance

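### The sarcopenia objective promises to find the essential components, but three nested arms identify only two packages: exercise, and the bundle added to it

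*Protocol*

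**What the plan says.** The secondary objective in section 2.0 is to "Determine which components of a functional rehabilitation program are essential to change the trajectory of sarcopenia", with muscle mass, strength and function named as the measures. The sarcopenia paragraph of the Introduction says the same: "we aim to understand which components of a functional rehabilitation program are essential".

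The design is in sections 4.5 and 4.6: "Participants will be randomized to one of three arms (control, group exercise only, multi-modal), with the intervention lasting 4-months".

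- **Arm 1** is control.
- **Arm 2** combines supervised group exercise, a tailored home programme and time set aside for socialising.
- **Arm 3** repeats the Arm 2 exercise unchanged and adds an oral nutritional supplement (ONS), a nutrition review with coaching, and a medication review. On the supplement it says "ONS will be provided to all participants unless contraindicated".
- **All arms** are to have vitamin D3.

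Table 1 is set out by individual component: social, vitamin D3, exercise, protein and medication.

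For muscle mass, section 4.8 allows DXA in up to 75 participants with sarcopenia, and "a subset of up to 36 participants will undergo an MRI scan in addition to DXA".

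**The concern.** To determine which components are essential is to claim attribution component by component, and Table 1 shows that the protocol itself thinks in individual components. The arms, however, add components in blocks. A gain in Arm 3 over Arm 2 could come from the supplement, the coaching, the medication review or any mixture of them, and the randomised data cannot say which. The same holds for group exercise, home exercise and social time within Arm 2.

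What is at stake is the conclusion the trial may draw on sarcopenia. With the objective as worded, a report that answers it would have to make a statement that randomisation does not support.

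**Working it through.** **1. The plan's own figure.** The protocol gives no sample size for the sarcopenia objective. Its only calculation on a primary outcome is for SPPB, Arm 3 against Arm 2 (section 5.0): difference 1, SD 2, alpha 0.05 (taken as two-sided), power 90%, drop-out 20%.

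- Normal formula: n = 2 × (1.960 + 1.282)² × 2² / 1² ≈ 84.1, so 85 per arm; 85 / 0.80 = 106.25, so 107 per arm and 321 in total.
- t-test version: 86 per arm; 86 / 0.80 = 107.5, so 108 per arm and 324 in total, which is the stated figure.

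The stated size reproduces. It concerns the whole added bundle, not any part of it.

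**2. What the arms identify.** Code each component 1 if the arm receives it (section 4.6).

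| | Group exercise (g) | Home exercise (h) | Social time (s) | ONS (o) | Nutrition review/coaching (c) | Medication review (m) | Vitamin D3 (v) |
|---|---|---|---|---|---|---|---|
| Arm 1 | 0 | 0 | 0 | 0 | 0 | 0 | 1 |
| Arm 2 | 1 | 1 | 1 | 0 | 0 | 0 | 1 |
| Arm 3 | 1 | 1 | 1 | 1 | 1 | 1 | 1 |

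With an intercept there are 8 columns, and the matrix has rank 3. Under an additive model, the assumption most favourable to the plan:

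- Arm 2 − Arm 1 = g + h + s
- Arm 3 − Arm 2 = o + c + m, on top of exercise

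Any observed difference D between Arms 3 and 2 fits (o, c, m) = (D, 0, 0), (0, D, 0) or (0, 0, D) equally well. Vitamin D3 cancels from both contrasts.

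The section on Arm 1 says that control receives none of the Table 1 interventions, whereas the section on all arms gives vitamin D3, a Table 1 item, to everyone. Those passages must be reconciled. The result here does not depend on how: if Arm 1 had no vitamin D3, v would merely join g + h + s in the first contrast, and the rank would still be 3, because it cannot exceed the number of arms.

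**3. What separation would take (illustration only).** Testing each of the three add-ons on top of exercise needs at least five arms: control, exercise, and exercise plus each add-on. At the stated 108 per arm that is 5 × 108 = 540. Spreading 324 over five arms gives 64.8 per arm, 64.8 × 0.80 ≈ 52 evaluable, and about 71% power for the 1-point SPPB difference. Even this would not split the exercise package.

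**4. Precision for muscle mass (a side note, not the size of the problem).** Assume the imaging subsets split equally over the arms, a two-sided 0.05 t-test at 80% power, and no baseline adjustment. The normal approximation is d = 2.802 × √(2/n); the t-test solution is slightly larger.

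| Subset | n per arm | d, normal | d, t-test |
|---|---|---|---|
| DXA, 75 / 3 | 25 | 0.79 | 0.81 |
| DXA after 20% loss | 20 | 0.89 | 0.91 |
| MRI, 36 / 3 | 12 | 1.14 | 1.20 |
| MRI after 20% loss | 9.6 | 1.28 | 1.36 |

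Adjusting for baseline multiplies d by √(1 − r²), where r is the baseline to 4-month correlation, which the protocol does not give. For 25 per arm, 0.81 becomes 0.70, 0.58, 0.49 and 0.35 at r = 0.5, 0.7, 0.8 and 0.9.

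**The case against.** **A narrower reading.** The protocol does not define components in either sentence. The Introduction frames the evidence gap as whether anything beyond exercise is needed, and faults an earlier multi-modal trial for being unable to isolate exercise. If the word means exercise, and what is added to exercise, the two contrasts answer the question. This has force, but it is the restated objective under another name. The present wording, next to Table 1, invites the component-by-component reading.

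**Component-level data are planned.** Log-books record home and group exercise, ONS, diet and vitamin D (4.7). Staff follow up whether medication recommendations were implemented (4.6, Arm 3). Adherence enters sub-analyses and the GEE models (4.9, 6.0 and Table 3). These can suggest which elements matter. They compare people who chose, or were able, to adhere with those who did not, so they cannot determine what is essential.

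**The imaging subsets.** A reader might infer from the caps of 75 and 36 that the sarcopenia objective fails for want of power, or that MRI must be reduced to a descriptive role. The documents do not support either. Low power is a separate matter from confounding. Table 2 attaches the caps to DXA and MRI only, while grip strength, chair stand, SPPB, Timed Up and Go and the 400 m walk are scheduled for participants generally, and the number who will screen positive for sarcopenia is not given. The detectable differences also shrink with baseline adjustment, which an analysis plan not shown here may specify.

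**Misuse of the result.** A reader might also infer that the sponsor means to credit an Arm 3 gain to one element, or to read a null imaging result as proof that a component is unnecessary. No passage says so.

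**Conclusion.** The objective, in section 2.0 and in the Introduction, claims a property that the design lacks. Two randomised contrasts are identified, the exercise package and the added bundle. None of the seven components coded above is isolated. This follows from the arm definitions alone, needs no assumption about effect size, and cannot be repaired by more participants in these arms or by an analysis plan.

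The reach is limited: one secondary objective and its echo. Randomisation, the primary outcomes and the sample size are unaffected. The detectable differences for muscle mass (about 0.81 to 0.91 for DXA and 1.20 to 1.36 for MRI) stand only as unadjusted illustrations under equal arms.

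**What to change.** Restate the objective in section 2.0 and in the Introduction. In participants with sarcopenia, estimate with 95% confidence intervals the effect on muscle mass, strength and function of:

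1. the exercise package of group exercise, home exercise and social time (Arm 2 minus Arm 1); and
2. the added bundle of ONS, nutrition review with coaching, and medication review (Arm 3 minus Arm 2).

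State that no randomised claim is made for any single component. Label analyses by adherence, or by whether medication recommendations were implemented, as exploratory and non-randomised.

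The cost is a protocol wording change and a less ambitious stated objective.
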